### Auditing {23}

During the delivery of treatment, the trainers are supervised separately according to the conditions. Supervision is provided by two experienced therapists who are independent of the trial management and sponsor.

### Protocol amendments {25}

An amendment to the protocol was submitted on 21 October 2023 to the Ethics Committee of the Paris-Lodron University of Salzburg to approve the cancellation of the control group and the payment of 50 Euro per participant. No further significant changes to the study protocol are expected. Therefore, there are no plans to communicate such changes to relevant parties.

### Confidentiality {27}

Personal information is collected, stored, and processed in a pseudonymous manner. Participants are helped to create their MS Teams account so that only their first name, not their last name, is visible to other participants. At the treatment’s beginning the trainers emphasise the need for confidentiality within the groups. Everyone involved in the project has signed a declaration of confidentiality regarding any personal information they become aware of.

### Dissemination policy {31 a-c, 33}

This study is part of a PhD project. It is therefore expected that the results of the study will be published in 2–3 papers in scientific journals. Participants can receive the results by e-mail on request.

The main authors of the study results are [name] (study management), [name] (main supervisor), [name] (co-supervisor), and [name].

It is not planned to use professional authors.

There are no plans for granting public access to the full protocol, participant-level data or statistical code. However, these data can be provided by the corresponding author upon request.

As this is a psychological therapy study, no biological samples will be collected. Accordingly, there are no plans to collect or store them.

## Discussion

### Strengths

The study design differs in many ways from other studies on shift work and sleep. First and foremost, the planned sample size of *N* = 142 will give the results more statistical power and thus significance. Due to the online implementation, the acquisition of participants does not have to be limited to the geographical area around the University of Salzburg but can be extended to the entire German-speaking area. In addition, all occupational groups with shift work are included, not just one occupational group, as is the case in many studies. This means that the results can be generalised to all shift workers.

Another strength is the design with two parallel groups: experimental and standard. The effectiveness of the new protocol can be directly compared with standard treatment. The applicability for shift workers and their acceptance can also be determined with this experimental design (drop-outs). Due to the difficulty of recruiting participants, there are several weeks between enrolment and the start of therapy for some participants. Although we do not have an explicit control group, we can still use the ISI data (pre-screening vs. pre-measurement) to check whether there has been spontaneous improvement without intervention.

The development of a specific manual can also be seen as a strength of this trail. Based on literature and the results of a preliminary study, factors that have a significant impact on the sleep of shift workers have been identified. Appropriate interventions were then selected and adapted. All interventions that had to do with regular schedules were removed in order not to jeopardise participant compliance.

However, what is innovative about this treatment manual is the implicit rationale for improving sleep. It is well known that an excessive focus on sleep disturbance can perpetuate the sleep disorder. However, most insomnia therapies focus on the disturbed sleep, thereby increasing the focus on the problem. In our manual, sleep is improved by reducing worry, anxiety, depressive rumination, etc. From the start of therapy, participants understand the key to better sleep: do not think about it and do not try to influence sleep.

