### Outcomes {12}

The primary outcome is improvement in the following key sleep variables: total sleep time, sleep onset latency, subjective sleep quality and daytime sleepiness. We also want to measure the severity of the sleep disorder.

Secondary outcomes are improvements in depressive mood and anxiety, dysfunctional sleep attitudes, and cognitive and physiological arousal.

Data will be collected at three time points: before starting treatment, at its end and 6 months later as a follow-up. We will compare group means between groups and within groups at each time point. Since we will have multiple primary outcomes over multiple time points, we will adjust the α-level using a Bonferroni correction.

The magnitude of the differences, especially in the pre-post comparisons, should not only be statistically, but also clinically significant. This means, for example, that subjects no longer meet the criteria for a sleep disorder (DSM-5, [11]) after treatment.

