#### Primary outcomes

PSQI: Pittsburgh Sleep Quality Index [40, 41]. This questionnaire measures sleep onset latency, total sleep time and subjective sleep quality. The re-test reliability is good, *r* = 0.82–0.89 [40], Cronbach’s *α* is also good with a value of 0.80 [41], the diagnostic validity is over 80% (sensitivity) or between 83 and 87% (specificity; quoted from [40]). So it can also be considered good.ESS: Epworth Sleepiness Scale [42], to measure daytime sleepiness. Cronbach’s α is acceptable to good with values between 0.73 and 0.88. According to Kendzerska et al. [43], re-test reliability is only described as good by one study with a value of *r* = 0.82, other studies found lower values. In their meta-analysis, Kendzerska et al. [43] found medium validity.ISI: Insomnia Severity Index [44], to assess severity of sleep disorder. According to [45], quality criteria are overall acceptable to good: Cronbach’s *α* = 0.74–0.78. In the opinion of these authors, further findings on concurrent validity and reliability are evidence that it is a valid and sensitive instrument.

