### Statistical methods {20 a-c}

For analysing primary and secondary outcomes, we will use linear mixed-models:

We will make within-subject comparisons of the primary and secondary outcomes at the three time points before and after treatment and at follow-up. We will also make between-subject comparisons, i.e., a comparison of the three conditions at the three time points.

Mediator and moderator analyses of the moderation and mediation of the outcomes: No hypotheses about mediators and moderators will be formulated. These analyses are purely exploratory.

We expect low attrition at the post-measurement, but somewhat higher at the follow-up measurement. Individuals who did not complete the post-measurement will be excluded. Those who did not complete only the follow-up may be included in the pre-post comparison but must be excluded from the calculations of the stability of the effects. Depending on their number, it may be necessary to analyse whether they represent a group with specific characteristics. As no post- or follow-up data is expected to be available from the dropouts, an intention-to-treat analysis is not possible. Instead, a per-protocol analysis will be conducted with all participants who were present in at least 4 sessions.

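### The pre-screening ISI score could sharpen the between-arm ISI comparison at almost no cost, but only if both pre-treatment scores are conditioned on

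*Protocol article*

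**What the plan says.** The Strengths subsection of the Discussion explains that, because recruitment is slow, "there are several weeks between enrolment and the start of therapy for some participants". It concedes "Although we do not have an explicit control group" and then says "we can still use the ISI data (pre-screening vs. pre-measurement) to check whether there has been spontaneous improvement without intervention". So an ISI score exists at pre-screening and another at the pre-measurement.

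The ISI has outcome status. The list of primary outcome instruments includes "ISI: Insomnia Severity Index [44], to assess severity of sleep disorder", and Outcomes {12} adds, after the four key sleep variables, "We also want to measure the severity of the sleep disorder".

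The outcome analysis rests on three occasions. Outcomes {12} states "Data will be collected at three time points: before starting treatment, at its end and 6 months later as a follow-up". Statistical methods {20 a-c} opens with "For analysing primary and secondary outcomes, we will use linear mixed-models" and plans "within-subject comparisons of the primary and secondary outcomes at the three time points before and after treatment and at follow-up", together with comparisons between conditions at those same times. Pre-screening is not one of the three occasions, no covariate is named, and the section does not say whether the pre-measurement enters as an outcome row or as a covariate.

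Data management {19} says that participants create their subject code at pre-screening, so the two scores can be linked. The planned check needs that link in any case.

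**The concern.** Two pre-treatment scores capture a person's usual insomnia severity with less error than one. The pre-screening score precedes treatment and cannot be affected by it, which makes it a legitimate baseline covariate. As described, it goes only to a before-after comparison with no control group, which cannot separate real improvement from regression to the mean. It contributes nothing to the comparison that randomisation protects.

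At stake is precision for one outcome. The confidence interval for the arm difference in ISI may be wider than the collected data allow. Precision is scarce in this trial: recruitment difficulty led to the cancellation of a third group, no dropout allowance is stated with the sample size, and participants without a post-measurement are excluded from analysis.

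**Working it through.** **Inputs from the document.** Sample size {14}: 2 groups, 3 times, effect f = 0.1, alpha 0.01, power 0.80, correlation 0.7, N = 142. Trial design {8}: equal allocation, so 71 per arm. Interventions {11a}: therapy groups of 12.

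**Step 1: the plan's own figure.** For the within-between interaction, the noncentrality is f² × N × m / (1 − r) = 0.01 × 142 × 3 / 0.3 = 14.2, with 2 and (142 − 2) × 2 = 280 degrees of freedom. Power at alpha 0.01 is 0.803, and 142 is the smallest even N that reaches 0.80. The stated N reproduces, so 0.7 is the planners' working correlation.

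**Step 2: variance of the arm contrast at post (t2), unit-variance scores, all correlations 0.7.** Each per-person variance below is multiplied by 2/71.

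- Pre-measurement (t1) kept as an outcome with arm means free: 2(1 − 0.7) = 0.600, giving 0.0169. Adding the pre-screening score as a main effect still gives 0.0169. A covariate with one slope shifts all of a person's rows equally and cancels from the change.
- Conditioning on t1 alone: 1 − 0.7² = 0.510, giving 0.0144.
- Conditioning on t1 and pre-screening: 1 − 2r²/(1 + r) = 1 − 0.98/1.7 = 0.424, giving 0.0119.

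The relevant comparison is the last two lines: 0.424/0.510 = 0.830, a 17% lower variance and a standard error about 9% smaller. The step from 0.600 to 0.510 comes from how t1 is handled and is not credited to the second score.

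**Step 3: sensitivity to the correlations.** Write a for the correlation of pre-screening with t1, b for pre-screening with t2, and c for t1 with t2. The residual variance is then 1 − (b² + c² − 2abc)/(1 − a²).

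| Assumption | t1 only | Both | Reduction |
|---|---|---|---|
| All 0.7 | 0.510 | 0.424 | 17% |
| All 0.6 | 0.640 | 0.550 | 14% |
| All 0.5 | 0.750 | 0.667 | 11% |
| b = 0.6, others 0.7 | 0.510 | 0.486 | about 5% |
| AR(1): b = 0.49, others 0.7 | 0.510 | 0.510 | 0% |

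If entry truncates the pre-screening score (assumed cuts from −0.5 to +1 SD, correlation 0.7 before selection), simulation gives a reduction of about 6% to 12%.

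**Step 4: clustering.** A participant-level covariate does not reduce variance between therapy groups. With an assumed residual intraclass correlation of 0.05, the group component is 0.510 × 0.05/0.95 = 0.0268, and times 12 it is 0.322. The ratio becomes (0.424 + 0.322)/(0.510 + 0.322) = 0.90, so the best case falls from 17% to about 10%. At 0.10 it falls to about 7%. The document gives no intraclass correlation.

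**Step 5: cost.** One further degree of freedom multiplies the variance by roughly 138/137 = 1.007 at N = 142, under 1%.

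**The case against.** The strongest objection is that covariates are usually listed in an analysis plan, which is not shown here. The Statistical methods section excludes none, and the sentence in Strengths is a discussion remark that contains no error. This stands in part. The only use known is the only use this article states, and a fuller plan might already cover the point. But the article does more than stay silent: it assigns the score a purpose and fixes the occasions on which the comparisons rest.

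The second objection is technical, and it stands in full. If t1 remains an outcome row with free arm means, entering the pre-screening score as a covariate leaves the arm-by-time contrast exactly as imprecise as before. Any recommendation must therefore say how t1 enters the model.

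The third also stands: 17% is a favourable case. The gap between the two scores is several weeks for some participants and varies, which argues for a weaker correlation of the earlier score with post-treatment ISI. Clustering lowers the gain further.

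A reader might also convert 17% into a trial-level claim: 142 × 0.510/0.424 is about 171 participants, or about 88% power for a contrast that would otherwise have 80% at alpha 0.01. The documents do not support this. N = 142 was derived for an interaction test on four outcome variables, namely the three PSQI measures and daytime sleepiness. The ISI is added to those, and no pre-screening score is described for any of the four.

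**Conclusion.** The point holds as a modest, low-cost improvement for the ISI alone. A second pre-treatment ISI score is collected and linkable, and the stated analysis leaves it out of the randomised comparison. Compared with conditioning on t1 alone, its use would lower the variance of the arm contrast at post by 17% at best under the protocol's own correlation of 0.7. The gain is 11% at 0.5, about 5% with mild decay, and nothing under AR(1) decay. All of these rest on assumed correlations and ignore clustering, which would reduce them. The figures are for the post-measurement; none was calculated for follow-up.

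The omission does not bias or invalidate anything, and no equivalent sample size or power should be claimed for the trial. The article also does not state the exact order of pre-screening, enrolment and allocation. That the score precedes treatment is clear, and the argument needs that.

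**What to change.** In Statistical methods {20 a-c}, state for the ISI only that the mixed model takes post and follow-up ISI as outcomes, with the pre-screening and pre-measurement ISI both entered as covariates whose slopes may differ by time. An equivalent choice is to enter both as pre-treatment time points, with means constrained equal between arms. Say explicitly which form is used. Do not simply add the pre-screening score as a main effect to a model that keeps the pre-measurement as an outcome with free arm means. Specify this before any post-treatment data are analysed, so that in an open-label trial there is no later choice between adjusted and unadjusted results.

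The cost is about one degree of freedom per outcome time and a linkage by subject code that the planned spontaneous-improvement check already needs. No further data collection or participant burden follows. If an analysis plan already specifies this, one confirming sentence is enough.

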### Limitations

A limitation of this study is that it is an online-only study. This decision was made under the impression of the corona pandemic, but also for purely practical reasons: 142 shift workers with sleep disorders are probably difficult to find in the Salzburg area, and face-to-face appointments plus travel could become a problem for shift workers. By opting for online delivery, we can extend the recruitment process nationally and save participants travel time.

However, there is a risk that less group cohesion will develop in this setting, especially if people come from completely different regions (e.g., North Rhine-Westphalia/Germany vs. Vorarlberg/Austria). There could be mentality and language problems here. The trainers are prepared for this during their training.

The inclusion of different professional groups has not only advantages. It is possible that the severity of the sleep disorder or the exact, individual symptoms differ between professions. An example is the police and fire services (sometimes traumatising) compared to manufacturing jobs (monotonous). This could affect both group dynamics and the effectiveness of therapy. The data need to be used to check whether subgroups need to be formed here.

Another limitation is the fact that the therapies are carried out by trained students. It would of course be better to use experienced psychotherapists with additional, specific training in sleep disorders. Unfortunately, this is not possible for financial reasons.

### Trial status

Protocol version 2, October 21, 2023.

Recruitment of participants began on July 13, 2023, and is expected to be completed by the end of the year.

## Data Availability

The study management and the project management will have access to the final trial data set. Pseudonymized data can be made available to other researchers upon request.

## Appendix

Informed consent materials {32}, see also study website [52].

## Abbreviations

CBT-I: Cognitive behavioural therapy for insomnia
CBT-I-S: Cognitive behavioural therapy for insomnia in shift workers
REM: Rapid eye movement (sleep stage)
DSM-5: Diagnostic and Statistical Manual of Mental Disorders
PSQI: Pittsburgh Sleep Quality Index
ESS: Epworth Sleepiness Scale
ISI: Insomnia Severity Index
HADS-D: Hospital Anxiety and Depression Scale
MZS: “Meinungen-zum-Schlaf-Fragebogen”
DBAS-16: Dysfunctional Beliefs and Attitudes about Sleep
PSAS: Pre-Sleep Arousal Scale
